##### Secondary End Points—Experience With the Simulator and Surgery—Collected at the End of Follow-up Training Weekend for Intervention Trainees 

Total number of times using the simulator over follow-up—collected from the BoneDoc AR appFrequency of using the simulator—collected from the BoneDoc AR appPerceived familiarity with SCHF by the end of the follow-up—determined from a 5-point Likert scale administered with a brief electronic survey:UnfamiliarSomewhat unfamiliarNeither familiar nor unfamiliarSomewhat familiarFamiliarTotal number of SCHF treatments undertaken over follow-up—calculated using the entries from trainee logbookNumber of mistakes while using the simulator—defined by the number of times the trainee reconsiders pin, collected from the BoneDoc AR appPinning accuracy on simulator—final pin and range of mistakes as calculated by the simulator—collected from the BoneDoc AR app

#### Patient Data

Data such as the National Health Index (NHI) number and surgical details will be collected from trainee logbooks. The following data will be collected from the corresponding DHB records: NHI number; time and date of presentation to the emergency department; age; sex; ethnicity; side of fracture; Gartland classification of fractures—type I, type II, type III, and type IV; the presence of consultant or any other assistants in surgery.

### Statistical Analysis

Operative outcomes using data taken before or without ongoing exposure to the simulator will be compared to outcomes using data from trainees who have used the simulator after 1 year. Comparisons will be performed using Student *t* tests or Wilcoxon Rank Sum tests (depending on the distribution of the data) for theater time and chi-square or Fischer exact tests (depending on the count of the outcome) for the number of complications, number of accurate pin placements, and number of mistakes.

Primary end points will be plotted on separate cumulative sum curves to show trends in performance over the course of follow-up by individuals and aggregated according to pre- and post–1-year simulator training. Control limits will be determined based on values identified in the literature and consultation with senior orthopedic consultants [22-24].

Accuracy of pin placements in subsets of images measured twice must be based on anterior-posterior, lateral, and oblique radiographs. Measurements taken will need to be compared for intra- and interobserver reliability using Bland-Altman plots and intraclass correlation scores.

The results from the familiarity questionnaire will be summarized as responses per category.

Univariable ordinary least squares regression analyses will be used to examine the association of theater time, number of complications (including nonideal unions), and number of x-ray shoots with independent variables. Logistic regression will be used to examine the association of accurate pin placement (yes or no) with independent variables. Independent variables will be the number of times the simulator is used, the number of SCHF procedures performed prior to intervention, Gartland classification, scores on tests of spatial awareness, and the number of SCHF procedures performed during the intervention. Independent variables that are significantly associated with a primary end point (*P*<.05) will be included as covariates in multivariable analyses. Appropriate model diagnostics, and where required, data transformations will be used.

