**Methods:**

This multicenter, interventional cohort study will involve orthopedic trainees from New Zealand in their first year of advanced training between 2019 and 2023. Advanced trainees with no simulator exposure who were in their first year in 2019-2021 will form the comparator cohort, while those in the years 2022-2023 will receive additional regular simulator training as the intervention cohort. The comparator cohort’s performance in pediatric SCHF surgery will be retrospectively audited using routinely collected operative outcomes and parameters over a 6-month period. Data on the performance of the intervention cohorts will be collected in the same way over a comparable period. The data collected for both groups will be used to determine whether additional training with an augmented reality training shows improved real-world surgical outcomes compared to traditional surgical training.

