### Study Overview

Appropriate validation of the BoneDoc AR simulator is necessary to determine its usefulness in surgical training. Transfer validity, the ultimate test of a surgical simulator, is the transfer of skills acquired on a simulator into the real-world operating theater. Validity tests are necessary to ensure the efficacy of a simulator in a training environment [19]. There are few surgical AR simulators, which have shown positive transfer validity, and none on AR simulators of SCHF treatment [20]. There is a clear paucity in the literature of this field, and there is a need for further research. This pilot study aims to examine the transfer validity of orthopedic trainee practice on the BoneDoc AR simulator.

We hypothesize that training with the simulator will improve in-theater performance as defined by a reduction of theater time, number of fluoroscopy images taken, postsurgical complication rates, and an increase in pinning accuracy. In all metrics, intervention trainees will be compared with retrospective-matched comparator trainees.

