### Eligibility Criteria

The inclusion criterion was being a full-time registered first-year orthopedic trainee in New Zealand between 2019 and 2023.

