### Recruitment

Intervention group trainees will be approached at training weekends to inform them about the study, to assess eligibility, and to receive consent. Comparator group trainees will be identified from the New Zealand Orthopaedic Association trainee registry and approached via email for this process. Enrollment for comparator group trainees will begin in February 2022, and enrollment for intervention group trainees will occur in the March training weekends of 2022 and 2023.

We aim to include data for 14 trainees in 2022; however, the number of trainees in 2023 is not yet known. The comparator cohort data will be retrospectively audited from trainees who undertook traditional training without exposure to the simulator during their 6 months of follow-up in the years 2019, 2020, and 2021 (n=41). We expect a total sample size of approximately 65 trainees, given an average of 12 new trainees per annum. The comparator group is matched based on their length of registered training at the start of follow-up, that is, first-year trainees with 2 months of registered training.

The in-theater performances of the comparator and intervention groups will be compared using cumulative sum charts for each of the primary outcomes to determine any differences in trends of skill acquisition according to the method of training. The simulator performance of the intervention group will be used to establish a learning curve and compared with in-theater learning curves.

Retrospectively matched trainees have been chosen instead of prospective randomized ones for the comparison group in order to maximize sample size and to avoid contamination. New Zealand only introduces 10-15 trainees per year into the orthopedic training program, and thus a prospective randomized trial will greatly limit the statistical power. There is also the chance of cross-group contamination as there is no way of ensuring comparator trainees located in the same area as intervention trainees will not use the simulator.

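### The Statistical Analysis defines the control side by simulator exposure instead of by the 2019–2021 cohort, so intervention trainees whose use lapses could be counted as controls

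*Protocol article*

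**What the plan says.** Three places in the protocol article fix the comparison by cohort.

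- Abstract, Methods: "Advanced trainees with no simulator exposure who were in their first year in 2019-2021 will form the comparator cohort". The trainees of 2022–2023 form the intervention cohort.
- Study Overview: "In all metrics, intervention trainees will be compared with retrospective-matched comparator trainees".
- Recruitment: the comparators are the 41 trainees of 2019, 2020 and 2021 "who undertook traditional training without exposure to the simulator during their 6 months of follow-up".

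The Statistical Analysis section fixes it by exposure status. The control side is given as "Operative outcomes using data taken before or without ongoing exposure to the simulator will be compared", and the other side as "outcomes using data from trainees who have used the simulator after 1 year". The cumulative sum curves are "aggregated according to pre- and post–1-year simulator training". Neither cohort is named in that section.

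**The concern.** The section that produces the result should select the same data as the sections that describe the design, and here it does not. Having no ongoing exposure is a weaker condition than having no exposure. A 2022–2023 trainee who tries the simulator and then stops meets the first condition and fails the second. If such a trainee's later cases move to the control side, three things follow:

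- The two sides share trainees, while the planned two-sample tests treat them as independent.
- Membership of a side depends partly on who kept practising, which may go with motivation, workload or skill.
- Exposed trainees enter the control data. Recruitment gives avoidance of contamination as one of its two reasons for using historical comparators, so the analysis wording would give up part of what that design choice was meant to secure.

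Since the article does not say which rule governs, the choice could also be made after the data are seen.

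**Working it through.** **Step 1: who meets each rule.** The rules were applied to four kinds of data.

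| Data | Abstract (cohort, no exposure) | Recruitment (cohort, none in follow-up) | Statistical Analysis (before, or not ongoing) |
|---|---|---|---|
| 2019–2021 trainee, never exposed | control | control | control |
| 2019–2021 trainee, exposed only outside follow-up (hypothetical) | excluded | control | control |
| 2022–2023 trainee, regular use | intervention | intervention | not control |
| 2022–2023 trainee, use stopped or lapsed | intervention | intervention | can be control |

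The last row is the substantive conflict. The second row is a minor difference between the Abstract and Recruitment.

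**Step 2: is the analysis wording only a paraphrase of the historical cohort?** Two features of the same section say it is not.

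- The cumulative sum curves are grouped by time on the simulator and not by cohort.
- The number of mistakes is among the outcomes to be compared. Secondary End Points defines mistakes as events during simulator use, recorded by the app for intervention trainees. The Comparators section says secondary outcomes are not collected for comparators. For this outcome the 2019–2021 cohort cannot be the control side, so any earlier data must come from the intervention trainees themselves.

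**Step 3: is lapsed use a realistic case?** Study Design and Intervention expect practice at least monthly. The plan sends monthly reminders, counts each trainee's uses, and enters the number of uses as an independent variable in the regressions. Variation in use is therefore anticipated. No lapse rate is given.

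**Step 4: the stated sample size.** The expected total is about 65 trainees, with 12 new trainees a year: 41 + 2 × 12 = 65. This reproduces the figure and implies about 24 intervention trainees.

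**Step 5: composition of the control side (illustration only).** Assume 24 intervention trainees, equal case rates per month, and an average of m of their 6 follow-up months reclassified as control. The share of control trainee-months that comes from intervention trainees is 24m / (41 × 6 + 24m).

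- m = 1: 24 / 270 = 8.9%
- m = 2: 48 / 294 = 16.3%
- m = 3: 72 / 318 = 22.6%

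The values of m are assumed. The result shows how the control side would be made up and is not an estimate of bias. Bias would also depend on how much benefit lapsed trainees keep and on how they differ from those who continue, and the article gives neither.

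**The case against.** The strongest reply is that the contrast is settled elsewhere. Study Overview commits to intervention versus retrospective comparators in every metric, Recruitment says the two groups' in-theater performances will be compared, and the Abstract assigns cohorts by calendar year. On that view the analysis sentence is a loose reference to the era before the simulator. This is a fair reading for theater time, pin accuracy and complications, and it is probably what was meant. It fails for simulator mistakes and does not fit the grouping of the cumulative sum curves, so the sentence cannot simply be read that way throughout.

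Several stronger inferences are tempting and are not supported.

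- *Intervention cases from before the March weekend would inflate the control times.* Study Design sets intervention follow-up at May to November, and the end-point heading limits primary outcomes to cases over follow-up. Outcomes of pre-March cases are not scheduled for collection. The difference-in-difference analysis under Strengths and Limitations is described as following both groups' learning curves over time and does not schedule them either.
- *Eligibility Criteria conflicts because it has no exposure rule.* Its single criterion ("The inclusion criterion was being a full-time registered first-year orthopedic trainee in New Zealand between 2019 and 2023") covers both cohorts, so a no-exposure rule there would exclude the intervention group.
- *The Abstract and Recruitment define materially different comparators.* They differ only for a 2019–2021 trainee exposed outside follow-up. The article reports no such trainee.
- *Every intervention case becomes control because none follows a full year of use.* March to November is about 8 months, so the one-year label does not fit the timeline. That is a separate wording problem, and the article does not say that cases before one year are to be analysed as control.

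**Conclusion.** The contradiction stands: the Statistical Analysis selects its control data by exposure status, and the Abstract, Study Overview and Recruitment select them by cohort. Followed literally, the analysis rule permits intervention trainees with lapsed use on the control side and the same trainee on both sides of tests for independent samples.

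Neither the size nor the direction of the resulting bias can be derived from the article. Retained benefit in lapsed trainees would shrink the contrast, while selection by adherence could move it either way. A reader might infer that the wording favours the simulator, but the article gives no basis for that. The practical effect would be nil if no trainee lapses or if the analysts follow the cohort definition. The point is therefore a correction that should be made, not evidence that the study's result will be wrong.

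**What to change.** In the Statistical Analysis:

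- Replace the exposure-based phrase with a cohort definition: the 2019–2021 comparator cohort, with no simulator use before or during follow-up, compared with the 2022–2023 intervention cohort.
- State that intervention trainees stay in their cohort whatever their adherence. The effect of the amount of use is already addressed by the planned regressions on number of uses.
- Aggregate the cumulative sum curves by cohort.
- Report any within-trainee comparison separately, including simulator mistakes, with a method that allows for repeated data on one trainee.

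Align Recruitment with the Abstract, so that both require no simulator use before or during follow-up. One question in the recruitment email would confirm it. Eligibility Criteria needs no change.

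The cost is wording plus that question. Any comparator found to have used the simulator earlier is excluded. The planned 41 versus about 24 is otherwise unchanged. Keeping low users in the intervention cohort means that the contrast estimates the effect of providing the simulator as it is actually used.

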### Study Design

The intervention cohort is composed of trainees using the BoneDoc AR simulator at least once per month over a follow-up period of 6 months (May to November) in the years 2022-2023 (Figure 1).

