### Interventions and Comparators

#### Intervention

The simulator will be first administered at the March training weekends for each year. We will use these training weekends to test participants at baseline on the simulator and collect demographic data via survey. The simulator will be set up as one of the 15-minute assessment stations in the training weekend. Simulator sets will be distributed to individual trainees following the training weekend. Upon delivery of the simulator sets, the principal investigator will also provide aid to the trainee in identifying an appropriate environment for the simulator and address any setup issues.

It is then expected that trainees will undertake, at minimum, monthly 15-minute practices on the simulator for the next 6 months of training. These practice data are sent to a cloud server after each use. Note that the simulator training will be in addition to any routine training they will receive at their respective hospitals. Over this time, primary end points for each in-theater case will be taken over the course of follow-up through District Health Board (DHB) records, including patient picture archiving and communication system (PACS) records and trainees’ logbooks.

We will request intervention trainees to write out relevant patient data and end point results as the cases present to maximize accuracy. Trainees will be reminded monthly by email to provide case data and practice on the simulator. Their simulator performance will be assessed again in a controlled environment during the November training weekend. At this point, secondary end points will also be collected via survey.

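### The between-group tests and the grouped CUSUM curves are cut at 1 year of simulator use, but follow-up lasts 6 months, so no planned case falls past the cut

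*Protocol article*

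**What the plan says.** Statistical Analysis in the protocol article sets up the two-group tests (t or Wilcoxon for theater time, chi-square or Fisher for the counts). The reference side is "Operative outcomes using data taken before or without ongoing exposure to the simulator", and these outcomes "will be compared to outcomes using data from trainees who have used the simulator after 1 year". The next paragraph plots the primary end points on CUSUM curves, by individual and "aggregated according to pre- and post–1-year simulator training".

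The design sections give a different time scale:

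- Study Design describes the intervention cohort as trainees using the simulator "at least once per month over a follow-up period of 6 months (May to November) in the years 2022-2023".
- Intervention states: "The simulator will be first administered at the March training weekends for each year". It then expects "monthly 15-minute practices on the simulator for the next 6 months of training", takes the in-theater end points during follow-up, and places the final assessment at the November weekend.
- The Abstract says the comparators' performance will be "retrospectively audited using routinely collected operative outcomes and parameters over a 6-month period", with intervention data gathered over a comparable period.
- Eligibility Criteria admits first-year trainees only.

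The Abstract, Study Overview and Recruitment state the main contrast as intervention cohort against retrospective comparator cohort. Recruitment says this applies to the CUSUM charts too. None of the three attaches a 1-year condition.

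**The concern.** Statistical Analysis is where the plan says which data stand on each side of the comparison, and there it uses a cut that the data collection cannot reach. The 1-year mark appears in both the two-group tests and the CUSUM grouping, so it is unlikely to be a slip in a single sentence.

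The study is nonrandomized with a historical comparator, so who is compared with whom, and over what period, should not be left to be inferred once the data are in. An analyst who follows the section literally has an empty exposed group. One who departs from it must choose a replacement definition that the section does not give. The regression models later in the section carry no 1-year condition and are not affected.

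**Working it through.** This is a calendar check; no power or sample-size formula applies. Months are days divided by 30.4375. The exact weekend dates are not given, so the range covers the earliest and latest days of the named months.

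**1. Reproduce the plan's own figure.** Follow-up from May to November (Study Design):

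- 1 May to 1 November: 184 / 30.4375 = 6.0 months. This agrees with the stated 6 months.
- Range: 31 May to 1 November is 154 / 30.4375 = 5.1 months; 1 May to 30 November is 213 / 30.4375 = 7.0 months.

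**2. Longest simulator exposure inside the data window.** First use in March, data collection closing in November (Intervention, Study Design):

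- Shortest: 31 March to 1 November is 215 / 30.4375 = 7.1 months.
- Longest: 1 March to 30 November is 274 / 30.4375 = 9.0 months.

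Counted over the stated practice or follow-up period instead, exposure is about 6 months.

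**3. Distance from the 1-year mark.** Twelve months after first use is March 2023 for the 2022 intake and March 2024 for the 2023 intake. The gap after follow-up closes is 12 − 9.0 = 3.0 to 12 − 7.1 = 4.9 months.

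**4. Planned cases past the mark.** End points are collected only during follow-up, and follow-up ends before month 12 in both intakes, so the number is 0. The 2024 completion date in the Abstract does not change this, because the article describes no in-theater collection after the 6 months.

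**5. The reference side.** Intervention follow-up starts in May and first use is in March. No operative window before exposure is scheduled for intervention trainees. The only scheduled unexposed data are those of the 2019-2021 comparators.

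**6. The two definitions side by side.**

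| | Statistical Analysis | Abstract, Study Overview, Recruitment |
|---|---|---|
| Exposed | after 1 year of use | 2022-2023 cohort |
| Reference | before, or without ongoing, exposure | 2019-2021 comparators |
| CUSUM grouping | before and after 1 year of simulator training | comparator and intervention groups (Recruitment) |
| Planned exposed cases | 0 | all intervention-cohort cases in follow-up |

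**The case against.** The strongest reply is that the 1-year wording is loose. It may mean the end of the training year or the time of analysis, and then the exposed group is not empty. An analyst who has read the Abstract, Study Overview and Recruitment would simply compare cohorts. Part of this stands. The intended contrast is stated elsewhere, and the empty group follows only from the literal reading. But nothing in the article gives the looser meaning, and the CUSUM phrase ties the year to simulator training itself. Even the looser reading leaves Statistical Analysis at odds with the 6-month period and the cohort contrast.

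Three stronger readings are tempting, and the article does not support them:

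- *Intervention trainees would sit on both sides of an unpaired test.* The word before in the reference definition invites this, but no pre-exposure operative data are scheduled for them. The phrase may simply describe the historical comparators.
- *Second-year data would be set against first-year comparators.* This would happen only if someone filled the empty group with later cases. Eligibility is limited to first-years, and end points are limited to follow-up.
- *Both cohorts are observed over the same 6 months.* The Abstract says only that the periods are comparable. Comparators starts follow-up in February, while Study Design starts the intervention cohort in May.

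That the article condenses a fuller protocol is no answer. Condensing explains missing detail, not a stated group definition that conflicts with the stated design.

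**Conclusion.** The contradiction holds. The 1-year cut in Statistical Analysis conflicts with the 6-month follow-up and with the cohort contrast stated elsewhere. Exposure within the planned data window is at most about 7 to 9 months, so on the literal reading 0 planned in-theater cases fall in the exposed group of the tests or in the post-1-year CUSUM group.

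This rests on two assumptions: that the year means duration of simulator use, and that nothing is collected beyond the described follow-up. If the first fails, the group is not empty but its definition is still unclear and inconsistent with the design. The study's data and its cohort design are not at fault. The error lies in the definition of the comparison, and it should be corrected before the cohorts are compared.

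**What to change.** In Statistical Analysis:

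1. Replace the opening sentence with: In-theater outcomes of the 2022-2023 intervention cohort during its 6-month follow-up will be compared with those of the 2019-2021 comparator cohort during its 6-month audit period. This also replaces the reference definition based on data before or without ongoing exposure.
2. Aggregate the CUSUM curves by cohort, as Recruitment already states, and drop the 1-year split. The individual curves stay as they are.

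Two related matters should not be settled silently by this rewording:

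- **Start of follow-up.** Study Design gives May, Comparators gives February, and Recruitment matches at 2 months of registered training. These need reconciling separately; calling the two periods equivalent would not do it.
- **Analysis population.** Study Design describes the intervention cohort as those using the simulator at least monthly. If the analysis is to include all enrolled 2022-2023 trainees whatever their use, that is a choice of analysis population and should be stated as one.

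The correction of the two definitions costs wording only, with no new data and no change in sample size. The population question needs a decision as well as a sentence.

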### Data Collection

#### Outcomes

##### Primary End Points—Collected for Each In-Theater Case Over Follow-up

Theater time and radiation time in seconds (radiation time may not be available from retrospectively assessed notes but will be attained where possible)—collected from procedure reports from electronic patient recordsNumber of fluoroscopy shots—collected from patient PACS recordsPin accuracy—accuracy is defined based on procedural recommendation literature—analyzed from patient PACS recordsComplication/nonideal union incidence—stratified for types of complications (nerve injury, vascular injury, loss of reduction, compartment syndrome, and infection)—collected from reviews of medical records and letters of referral from electronic patient notes

These primary end points have been determined as measurements of trainee performance, which are relatively easily retrieved from patient records and trainee logbooks.

The number of fluoroscopy shots and radiation time can be used to approximate the amount of radiation patients and staff are exposed to. In particular, for patients, theater time and radiation exposure have been shown to correlate to a higher chance of complications and thus should be avoided [21]. Studies have shown a decrease in both measurements for SCHF treatments with increased trainee proficiency [22,23]. Pin accuracy affects the stability of union, and there are well-established guidelines for ideal position of pins.

Ultimately, postoperative complications and nonideal union are the most crucial outcomes the trainees should aim to avoid. We do not expect to see high rates of these for either group, but overall rates will be monitored for comparison.

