## Results

As of February 2022, a total of 8 retrospective comparators have been recruited by email.

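### Theater time is compared by a Student t or Wilcoxon test picked from the observed data, so the effect measure is not fixed and the t option assumes equal spread in cohorts of about 41 and 24

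*Protocol article*

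**What the plan says.** The Statistical Analysis section of the protocol article says "Comparisons will be performed using Student" t "tests or Wilcoxon Rank Sum tests (depending on the distribution of the data) for theater time". No criterion for judging the distribution, no default test and no effect measure is given. The same section plans ordinary least squares regressions of theater time. Its sentence on diagnostics and transformations closes that regression paragraph and is not attached to the two-group test.

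Theater time heads the list of primary end points, which are "Collected for Each In-Theater Case Over Follow-up". The Recruitment section gives 41 comparators from 2019 to 2021 and says "We expect a total sample size of approximately 65 trainees, given an average of 12 new trainees per annum". On the intervention side it says "We aim to include data for 14 trainees in 2022; however, the number of trainees in 2023 is not yet known".

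A 5% threshold appears only in the rule for choosing covariates, "Independent variables that are significantly associated with a primary end point". No significance level is stated for the comparison of cohorts.

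**The concern.** There are two separate problems.

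The first is the quantity being estimated. A t test compares means and gives a difference in time units. A Wilcoxon test compares ranks and by itself gives a P value with no difference attached. When the choice waits for the data, so does the meaning of the result. If Wilcoxon is chosen, the group comparison also no longer matches the mean-scale regression planned for the same outcome. A pilot should hand one estimate with an interval to the next study.

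The second is the equal-variance assumption. Student's t is sensitive to unequal spread when group sizes differ. In a randomised trial with no effect, both arms share one distribution and the assumption holds under the null. These cohorts are historical and concurrent, so their spreads can differ even if the simulator does nothing. Comparators span three training years and intervention trainees two. Comparator follow-up starts in February, while the intervention cohort runs from May to November. Comparator data are audited retrospectively, while intervention trainees are asked to record case results as they occur. None of this shows that the spreads differ or in which direction, but nothing in the design makes them equal.

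**Working it through.** **Group sizes.** 41 comparators plus two intakes of 12 gives 41 + 2 × 12 = 65, which reproduces the planned total. About 24 intervention trainees are therefore implied. Using the 14 expected in 2022 instead gives 41 + 14 + 12 = 67, with 26 in the intervention cohort, which is still close to the stated approximate total.

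**Assumptions not in the article.** Two-sided 5% level; one value per trainee; normal data; ratio r of intervention SD to comparator SD between 0.5 and 2.

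**Large-sample level of Student's t.** Set the comparator SD to 1, with n₁ = 41 and n₂ = 24.

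- True variance of the mean difference: V = 1/41 + r²/24
- Variance that the pooled test uses: P = [(40 + 23r²)/63] × (1/41 + 1/24)
- Actual level: 2 × [1 − Φ(1.96 × √(P/V))]

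At r = 2: V = 0.0244 + 0.1667 = 0.1911; P = (132/63) × 0.0661 = 0.1384; √(P/V) = 0.851; level = 2 × [1 − Φ(1.668)] = 9.5%.

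At r = 0.5: V = 0.0244 + 0.0104 = 0.0348; P = (45.75/63) × 0.0661 = 0.0480; √(P/V) = 1.174; level = 2 × [1 − Φ(2.301)] = 2.1%.

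**Simulation check.** Student and Welch: 400,000 trials per ratio. Wilcoxon: 40,000 per ratio.

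| SD ratio | Student, formula | Student, simulated | Welch, simulated | Wilcoxon, simulated |
|---|---|---|---|---|
| 0.5 | 2.1% | 2.3% | 5.0% | 3.8% |
| 0.67 | 3.0% | 3.1% | 5.0% | 4.0% |
| 1 | 5.0% | 5.0% | 5.0% | 4.8% |
| 1.5 | 7.7% | 7.6% | 5.0% | 6.6% |
| 2 | 9.5% | 9.6% | 5.0% | 7.8% |

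**Role of the imbalance.** With near-equal groups (33 and 32), Student's t stays between 4.8% and 5.3% over the same ratios. The distortion needs both unequal sizes and unequal spread.

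**The data-driven choice.** The article gives no criterion, so a Shapiro-Wilk test in each group was assumed (8,000 trials per setting, 41 versus 24). It sent the analysis to Wilcoxon in about 10% of trials with normal data, 73% to 74% with gamma data and 84% with lognormal data. With equal spread, the two-step rule rejected in 5.3% to 5.4% of trials, so choosing from the data adds little error by itself. With skewed data and unequal spread but equal means, it rejected in 7.5% to 13.4%. Part of that excess arises because Wilcoxon does not test equality of means, which is the effect-measure problem again.

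**Price of Welch when it is not needed.** With equal SDs and a true difference of 0.5 SD, simulated power is 48.4% for Student and 48.0% for Welch. At 0.75 SD it is 82.0% and 81.6% (200,000 trials each).

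**The case against.** The strongest reply is that the harm is hypothetical. The article reports no SDs. At equal spread every option holds its level, and if simulator trainees became more uniform the planned t test would be conservative. Inflation at 41 versus 24 needs the intervention cohort to be the more variable one, and the article gives no reason to expect that. All of this stands, and it limits what can be said about size.

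A second reply is that every figure treats a trainee as one observation, while outcomes are collected per case. If cases were compared directly, the group sizes and their ratio would be unknown and repeated cases within a trainee would matter as well. This also stands. It qualifies the figures and shapes the fix.

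A third is that the variance option and the effect measure are usual analysis-plan detail, and that Student may be loose wording for any t test. This stands only in part. Silence would be no finding, but the article states a rule under which the data choose the test. If Welch is meant, saying so settles the variance part and leaves the effect measure open.

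Three stronger readings are tempting and are not supported.

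- A reader might infer that a stated 5% level is breached. No level is stated for this comparison, so 5% is only a nominal assumption here.
- A reader might set the early count, "As of February 2022, a total of 8 retrospective comparators have been recruited by email", against 24 intervention trainees and obtain far worse error rates. Comparator enrollment was due to begin in that same month and 41 are planned, so the count is an early status report and not the design.
- A reader might infer a material loss of power from choosing the test after seeing the data. Under an assumed lognormal model with log SD 0.45 and a 20% reduction, power was 46.5% for the look-then-choose rule and 47.9% for a fixed log-scale Welch test. That gap is too small to act on.

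**Conclusion.** The point holds in a limited form. That the estimand depends on the data follows directly from the text and needs no assumption about spread. The equal-variance weakness is conditional: with one normally distributed value per trainee, 41 versus 24 and a nominal two-sided 5% level, Student's t runs from about 2.3% to 9.6% as the SD ratio goes from 0.5 to 2, against about 5% for Welch. At equal SDs there is no distortion, and the article does not allow the true ratio to be judged. Switching to Wilcoxon does not remove the sensitivity, since its level moves from 3.8% to 7.8% over the same range. The change is worth making because a primary end point is affected and the remedy is nearly free, not because a large error has been shown.

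**What to change.** Replace the choose-by-distribution rule for theater time with one prespecified comparison that does not assume equal variances. It can be Welch's test on one summary value per trainee, or a model of case-level times that accounts for cases within trainee. State which. A plain two-sample test on all cases would ignore the repeated cases and should not be used.

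Name one effect estimate with a 95% CI, on a scale fixed before outcome data are seen: a difference in minutes, or a ratio of geometric means if log time is used. Either is acceptable. The log scale also gives no difference in minutes, so it is a choice to justify on clinical grounds or from outside data. Use the same scale in the planned regression of theater time. Keep Wilcoxon as a labelled sensitivity analysis.

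The Welch version costs a few sentences and runs in R, the planned software. The case-level model takes somewhat more specification. If the variances are in fact equal, the loss with Welch is about 0.4 percentage points of power in the cases checked.
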